## Abstract

**Background:**

Hepatocellular carcinoma is the sixth most common malignancy in the world. Major hepatectomy (resection of greater than or equal to three liver segments) is needed if a tumour is large or close to major blood vessels. Despite low mortality, open major hepatectomy is associated with high rates of tumour recurrence that limits survival. Laparoscopic major hepatectomy has been proposed as an alternative approach with potential oncological benefits. This study compares laparoscopic major hepatectomy with open major hepatectomy for hepatocellular carcinoma in a randomized trial.

**Methods:**

The Asia-Pacific multicentre randomized trial of laparoscopic *versus* open major hepatectomy for hepatocellular carcinoma (AP-LAPO trial) is an open-labelled multicentre randomized trial to be conducted in five centres in the Asia-Pacific region. The study will test the hypothesis that laparoscopic major hepatectomy for hepatocellular carcinoma is associated with less tumour recurrence and better survival compared with open major hepatectomy; the primary outcome being 2-year recurrence-free survival. Secondary outcomes include hospital mortality, postoperative complications according to the Clavien–Dindo classification, time to functional recovery, quality of life, long-term survival, and postoperative serum surgical stress-related cytokines.

**Results and conclusion:**

The AP-LAPO trial will determine whether laparoscopic major hepatectomy offers oncological benefits to patients with hepatocellular carcinoma compared with open major hepatectomy.

**Registration number:**

NCT04852211 (http://www.clinicaltrials.gov) registered on 21 April 2021

**Protocol version:**

AP-LAPO trial version 01 (1 December 2021)

## Introduction

Hepatocellular carcinoma (HCC) is the sixth most common malignancy in the world^1^. The practice of screening by ultrasonography and serum *α*-fetoprotein concentration in cirrhotic patients and hepatitis B carriers has led to an increasing incidence of HCC^2^. Curative treatment options for patients with early HCC include hepatic resection, local ablation, and liver transplantation. Hepatectomy remains the mainstay treatment for patients with HCC and non-cirrhotic liver according to European Association for the Study of the Liver (EASL), American Association for the Study of Liver Diseases (AASLD), and ESMO guidelines^3–5^.

Open major hepatectomy (OMH) (resection of greater than or equal to three liver segments) is indicated for large tumours (greater than 5 cm) that are centrally located and/or close to intrahepatic major vessels. OMH is associated with significant morbidity (about 30 per cent), though hospital mortality has been reduced to less than 5 per cent^6^. Wound and pulmonary complications are the most common early complications, but intrahepatic tumour recurrence remains a major problem in up to 50 per cent of patients^7^.

Laparoscopic major hepatectomy (LMH) has become a feasible and effective approach for the surgical management of HCC^8^. LMH seems to be associated with less surgical stress and manipulation of the tumour during surgery^9^, without increasing blood loss, morbidity, and mortality^10^. These potential benefits might lead to long-term survival benefit^11^ and better quality of life for patients. LMH and OMH have been compared in retrospective matching analyses^8,12^. The aim of this multicentre RCT is to compare LMH and OMH for HCC. The primary outcome is recurrence-free survival.

## Methods

The Asia-Pacific multicentre randomized trial of laparoscopic *versus* open major hepatectomy for hepatocellular carcinoma (AP-LAPO trial) is an open-labelled randomized trial to be conducted in five Asia-Pacific centres (Department of Surgery, The Chinese University of Hong Kong; Department of Surgery, Kwong Wah Hospital, Hong Kong; Department of Surgery, The First People Hospital of Foshan, China; Department of Biliary Surgery, Eastern Hepatobiliary Surgery Hospital & Institute, Second Military Medical University, China; Department of Surgery, Department of Surgery, West China Medical School of Sichuan University). The trial has been registered at ClinicalTrials.gov of the US National Library of Medicine (NCT04852211). The trial protocol follows the Standard Protocol Items: Recommendations for Interventional Trials (SPIRIT) guideline^13^. The coordinating centre for the trial is the Department of Surgery, The Chinese University of Hong Kong. The trial is free of industrial sponsorship.

### Eligibility criteria

Surgical procedures will be carried out by senior hepatobiliary surgeons. According to the international standard for laparoscopic liver surgery, each surgeon will need to have performed at least 55 resections classified as LMH to be included in the study^14,15^.

Inclusion criteria consist of: a diagnosis of HCC as defined by the EASL^16^; tumour size less than or equal to 8 cm or in the case of multiple nodules in a single lobe the sum of the greatest diameter of all nodules less than or equal to 8 cm^12,17,18^; tumour suitable for both LMH and OMH requiring resection of greater than or equal to three Couinaud’s segments as agreed by the hepatobiliary multidisciplinary team; absence of extrahepatic metastasis or radiological evidence of invasion of portal vein or hepatic vein branches; Child A liver function; indocyanine green retention at 15 min (ICG-15) less than or equal to 15 per cent; adequate future liver remnant based on image-guided volumetry greater than or equal to 35 per cent of estimated standard liver volume; and patient fit for general anaesthesia and major liver resection.

Exclusion criteria involve: previous treatment for HCC (for example transarterial chemoembolization or chemotherapy) and tumours requiring combined hepatectomy and thermal ablation therapy. Patients will also be excluded at the time of surgery (dropout) if there is: bilobar liver involvement; unexpected portal vein invasion and peritoneal metastasis not identified at preoperative imaging; liver remnant smaller than expected; or in both laparoscopic and open groups where the operating surgeon decides to abort the procedure due to locally advanced tumour condition before starting the resection phase. The patient flow chart is shown in *Fig. 1*.

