### Measurements

Intraoperative: operative time (measured from time of skin incision to wound suturing); blood loss; blood transfusion volumes and other blood products (platelet concentrate, fresh frozen plasma); intraoperative major events (hypotension for greater than 20 min and use of inotropes); and laparoscopic to open conversion. The conversion is defined as the change of surgical approach during the resection phase of major hepatectomy, when the operating surgeon encounters technical difficulty. Patients undergoing conversion will be included in the laparoscopic group and be analysed on an ‘intention-to-treat’ basis.

Postoperative: liver biochemistry and coagulation profile on postoperative days 1, 3, 7, and day of discharge; postoperative morbidities according to Clavien–Dindo classification^22^; 30-day, 90-day, and in-hospital mortality; length of ICU and hospital stay; hospital readmission (90 days after discharge); and time to functional recovery (defined as independently mobile at the preoperative level, sufficient pain control with oral medication alone, ability to maintain at least 50 per cent daily caloric intake, no intravenous fluid administration, and no clinical signs of infection)^23^.

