### Sample size

Based on a reported 2-year recurrence-free survival rate of 72 per cent after OMH^12^ and an expected 88 per cent after LMH according to a previously reported series^8^, 150 patients need to be recruited to each arm to demonstrate a statistically significant difference with 80 per cent power at the 0.050 level of two-sided significant difference between LMH and OMH^24^. Allowing a 10 per cent dropout rate, 165 patients will be recruited in each arm. This sample size will allow detection of a reduction of 2-year tumour recurrence from 50 per cent in the OMH group to 30 per cent in the LMH group with a similar power and level of significance. Secondary outcomes will be interpreted for hypothesis-generating only.

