### Randomization

Preoperative randomization will be adopted on the day of admission. A total of 330 subjects will be allocated 1:1 to either the LMH group or the OMH group. The randomization schedule will be generated by the Clinical Trials Centre (CTC) of the principal investigator’s centre, prior to the start of the study. Stratified block randomization (block size of 10) will be used to ensure treatment allocation in equal proportions at each centre. The randomization list will be kept in a set of tamper-evident envelopes. The envelopes will be identical and sealed. The trial identifier with a sequential number will be printed on each envelope. Envelopes will be unsealed to reveal the allocation treatment 1 day prior to surgery.

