### Blinding

There will be no blinding for all recruited patients, investigators, operating surgeons, and other supporting staff.

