### Interim analyses

Patient recruitment status will be reviewed every 4 months in planned investigator meetings in which interim analyses will be carried out. If the accrual rate is slower than expected, the principal investigator and co-investigators will discuss the possible reasons and ways to improve the recruitment rate. The interim analyses will not be affected by the results. A data-monitoring group will consist of two independent, external experts who will be responsible for monitoring the progress of the study. If there are significantly more serious adverse events associated with either group after 1 year of commencement of the study, the trial will be terminated as decided by the principal investigator and the data-monitoring group. The same will be applied to the situation where the difference in tumour recurrence between groups is significantly less than expected. The final analysis of the trial will be carried out on an intention-to-treat basis.

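### Randomised patients are excluded as dropouts on findings at surgery or on an unblinded decision to abort, which conflicts with the intention-to-treat analysis the protocol promises

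*Protocol article*

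**What the plan says.** **Timing.** Protocol article, Randomization: "Preoperative randomization will be adopted on the day of admission", and "Envelopes will be unsealed to reveal the allocation treatment 1 day prior to surgery". The surgeon therefore knows the arm before operating, and the section on Blinding confirms that the trial is open: "There will be no blinding for all recruited patients, investigators, operating surgeons, and other supporting staff".

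**Removal at surgery.** Eligibility criteria, in the paragraph on exclusions: "Patients will also be excluded at the time of surgery (dropout) if there is: bilobar liver involvement". The list continues with portal vein or peritoneal spread that imaging had missed, a remnant smaller than expected, and cases in either arm where "the operating surgeon decides to abort the procedure due to locally advanced tumour condition before starting the resection phase".

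**Allowance.** Sample size: "Allowing a 10 per cent dropout rate, 165 patients will be recruited in each arm".

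**Analysis population.** Interim analyses: "The final analysis of the trial will be carried out on an intention-to-treat basis". The Measurements section also applies intention to treat to patients converted from laparoscopic to open surgery, where "The conversion is defined as the change of surgical approach during the resection phase of major hepatectomy".

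Nothing in the article says that patients excluded at surgery remain in the primary analysis or continue to be followed.

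**The concern.** Every trigger for removal is seen after allocation, through the allocated approach, by a surgeon who knows the arm. Laparoscopic and open exploration need not reveal the same disease or lead to the same decision to abort. A patient excluded on these grounds is not analysed as randomised, so the exclusion rule and the intention-to-treat statement pull in opposite directions.

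The primary outcome is at stake. Several of the removal reasons denote more advanced disease, so removed patients probably have poorer RFS than the rest. If one arm loses more of them, its remaining patients look better with no treatment effect at all. If these patients are also not followed, their outcomes cannot be reliably recovered later.

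**Working it through.** **The plan's own figure.** 150 × 1.10 = 165 per arm. The allowance uses the same word, dropout, as the exclusion rule, and no other use of the word in the article separates the two.

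**The statements in order of time.**
1. Randomise on the day of admission.
2. Open the envelope the day before surgery.
3. Explore by the allocated approach.
4. Exclude as dropout on operative findings or a decision to abort.
5. Analyse by intention to treat.

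Step 4, read as removal from the study, cannot be squared with step 5.

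**Size if removal is unequal.** From the plan: 165 per arm and RFS of 72%, here taken as true in both arms (no effect). Assumed, because the documents do not give them: the fraction removed in each arm (*e*), and the 2-year RFS of removed patients (*r*), taken from 40% down to 0%.

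- Analysed RFS = (0.72 − *e* × *r*) / (1 − *e*)
- Analysed number = 165 × (1 − *e*)
- Chance of a significant result favouring the arm with more removals = Φ[(*d* − 1.96 × SE₀) / SE₁], where *d* is the difference in analysed RFS, SE₀ the pooled and SE₁ the unpooled standard error. This is a two-proportion test at 2 years, used as an approximation to the planned log rank test. With no bias the chance is 2.5%.

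Worked example, 10% v 2% removed and *r* = 0:
- 0.72/0.90 = 80.0% (n = 148.5) and 0.72/0.98 = 73.5% (n = 161.7), so *d* = 6.5 points
- SE₀ = 0.0481 and SE₁ = 0.0478
- (0.0653 − 1.96 × 0.0481)/0.0478 = −0.61, and Φ = 27.2%

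The same with *r* = 40%: (0.72 − 0.04)/0.90 = 75.6% and (0.72 − 0.008)/0.98 = 72.7%, so *d* = 2.9 points and the chance is 8.4%.

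| Removed, one arm v other | False difference (*r* = 40% to 0%) | Chance of false significance |
|---|---|---|
| 10% v 2% | 2.9 to 6.5 points | 8.4% to 27.2% |
| 10% v 5% | 1.9 to 4.2 points | 5.6% to 14.0% |
| 5% v 3% | 0.7 to 1.6 points | 3.4% to 5.1% |
| 10% v 10% | 0 | 2.5% |

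The table is symmetric: either arm could be the one with more removals. Equal removal of 10% leaves no false difference but raises RFS in both arms from 72% to between 75.6% and 80.0%.

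**Power if everyone is kept.** Take the plan's 72% v 88% as RFS among resected patients, and count unresected patients as failures, with 165 per arm:
- 5% unresected per arm: 0.72 × 0.95 = 68.4% v 0.88 × 0.95 = 83.6%; power 90.2%.
- 10% unresected per arm: 64.8% v 79.2%; power 83.3%.

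**The case against.** **The conflict may be one of wording only.** The exclusion rule never says that patients leave the analysis. Dropout could mean off the allocated procedure, with the intention-to-treat sentence governing the final analysis. The section points to a flow chart that is not available here and might settle this. So a reader who infers that the analysis will certainly omit these patients goes further than the text. The objection does not remove the problem: the rule speaks of exclusion, sits among the exclusion criteria and shares its term with the sample size allowance. A site or analyst could fairly read it as removal and stop follow-up.

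**Safeguards against unequal removal exist.** The abort rule covers both arms and only the period before resection. The multidisciplinary team must agree that the tumour suits both approaches. Volumetry must show a remnant of at least 35%, imaging must show no vascular invasion, and each surgeon must have performed at least 55 laparoscopic major resections. These reduce the risk of unequal removal but do not exclude it. They do make 10% v 2% an extreme case rather than a forecast.

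**Three stronger readings are not supported.**
- *A false-positive risk of 27%, in favour of laparoscopy.* This needs very unequal removal and no 2-year RFS in any removed patient. The documents support neither, nor a direction.
- *All removed patients have the worst prognosis.* A small remnant concerns liver volume rather than tumour stage, and no outcome is given for any removed group.
- *A switch to open surgery before the resection phase escapes intention to treat.* It falls outside the definition of conversion, but if the tumour is then resected it meets no exclusion reason, and the general intention-to-treat sentence keeps it in the laparoscopic arm. At most, the descriptive conversion rate is affected.

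**Conclusion.** The point holds as a conflict between the Eligibility criteria and Interim analyses sections, reinforced by the dropout allowance under Sample size. It needs correction because it decides who is in the primary analysis of an open-label trial.

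The bias is possible, not demonstrated. It requires removal to differ by arm and removed patients to have different RFS from the rest. Across the scenarios shown, the false difference runs from 0.7 to 6.5 points, and the chance of a significant result favouring the arm with more removals from about 3% to 27%, against 2.5%. These ranges rest on assumed removal rates and on assumed RFS of 40% to 0% in removed patients. With equal removal there is no false difference, only RFS that looks too favourable in both arms.

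**What to change.** In Eligibility criteria, replace exclusion as dropout with a statement that patients found unresectable, or whose procedure is aborted, stay in the primary analysis in their allocated arm and are followed for recurrence and survival. This concerns analysis and follow-up only. The surgical grounds for aborting are not at issue.

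Also:
- Fix in advance one rule, the same in both arms, for how an unresected patient counts in RFS. An event on the day of surgery is one option; what matters is that the rule is set beforehand.
- Report the number of unresected patients and the reasons by arm.
- Give the resected-only set as a sensitivity analysis.
- State that any change from laparoscopic to open, including before the resection phase, is analysed in the laparoscopic arm. No new definition of conversion is needed.

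**Cost.** Amended wording and follow-up of a few unresected patients. If they count as failures, RFS will be slightly less favourable in both arms. Under the plan's 72% v 88%, 165 per arm still gives about 90% power with 5% unresected per arm and 83% with 10%, so no extra enrolment is needed in these scenarios.

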**Fig. 1 zrac166-F1:**
[figure not shown]
Patient flow chart LMH, laparoscopic major hepatectomy; OMH, open major hepatectomy

### Intervention

Preoperatively all patients will undergo: blood tests (complete blood count, liver and renal function, coagulation profile, serum *α*-fetoprotein level, and hepatitis B and C serology); radiological imaging (chest X-ray, CT scan, or MRI to assess tumour size, number, location, and image-guided volumetry of future liver remnant); ICG-15 test^19^; and quality of life assessment using a Chinese version of the Functional Assessment of Cancer Therapy-General (FACT-G) questionnaires.

All patients will receive prophylactic antibiotics (Augmentin (amoxicillin + clavulanate) (GlaxoSmithKline) 1.2 g intravenously for one dose or levofloxacin (Daiichi Sankyo) 500 mg intravenously for one dose in case of penicillin allergy) and proton pump inhibitor (pantoprazole (Takeda) 20 mg intravenously for one dose). The surgical intervention will be performed under general anaesthesia.

### Interventions: LMH

For the LMH group, the patient will be placed in a left semi-decubitus position. Pneumoperitoneum will be created by carbon dioxide insufflation and the intra-abdominal pressure maintained at 13–15 mmHg. In addition to the camera port (10 mm), two 12-mm and two 5-mm ports will be used and adjusted according to tumour location and extent of resection. Laparoscopic ultrasonography will be used to confirm tumour location and guide liver transection. The extent of resection will depend on tumour location. Cholecystectomy will be performed. The anterior approach for major hepatectomy will be routinely adopted^20^. Following liver hilum dissection to divide the appropriate hepatic artery and portal vein, liver transection will be performed using a combination of ultrasonic dissecting shears (Harmonic scalpel^®^, BBT Medical, Wuhan, China), a vessel sealing system (Ligasure^®^, Medtronic, Minneapolis, MN, USA), radiofrequency energy (TissueLink^®^, Nissha Medical Technologies, Buffalo, NY, USA), and a laparoscopic-adopted Cavitron Ultrasonic Surgical Aspirator (CUSA^®^, Soma Tech, Bloomfield, CT, USA) as determined by the operating surgeon. For vessels greater than 5 mm in diameter, Hem-o-lock or titanium clips will be used. An intermittent Pringle manoeuvre (20 min with 5 min rest for one cycle) will be selectively applied depending on intraoperative haemostasis. The central venous pressure will be routinely kept below 5 mmHg. The hepatic vein and portal pedicles will be transacted by laparoscopic linear stapler. The specimen will be retrieved through a protected wound using Pfannenstiel incision at the suprapubic region. An abdominal drain will be selectively placed on the liver transection surface according to the operating surgeon.

### Intervention: OMH

For the OMH group, resection of the tumour will be performed as previously described^21^. The patient will be placed in a supine position. Laparotomy will be by ‘Mercedes-Benz’ incision. Cholecystectomy will be carried out. Either an anterior or a conventional approach will be adopted according to the preference of the operating surgeon^20^. Hilar dissection to divide the appropriate hepatic artery and portal vein will be performed. Liver transection will be performed using a CUSA^®^ or ultrasonic dissecting shears. Sutures, titanium clips, and vascular staplers will be used to achieve haemostasis. An intermittent Pringle manoeuvre will be selectively adopted. An abdominal drain will be placed according to the operating surgeon.

### Outcomes

#### Primary outcome

The primary outcome is 2-year recurrence-free survival.

#### Secondary outcomes

These include 30-day, 90-day, and in-hospital mortality, postoperative complications, quality of life, time to functional recovery, 2-year overall survival, 5-year overall survival, and recurrence-free survival. Surgical stress-related cytokines serum interleukin 6 (IL-6) and immunosuppressive acidic protein (IAP) will be measured before surgery and on postoperative days 1 and 7. Measurement of IL-6 and IAP levels will be performed by immunoassay using commercially available kits (MILLIPLEX^®^ MAP Human Cytokine/Chemokine Magnetic Bead Panel, Merck Ltd, Rahway, NJ, USA).

### Measurements

Intraoperative: operative time (measured from time of skin incision to wound suturing); blood loss; blood transfusion volumes and other blood products (platelet concentrate, fresh frozen plasma); intraoperative major events (hypotension for greater than 20 min and use of inotropes); and laparoscopic to open conversion. The conversion is defined as the change of surgical approach during the resection phase of major hepatectomy, when the operating surgeon encounters technical difficulty. Patients undergoing conversion will be included in the laparoscopic group and be analysed on an ‘intention-to-treat’ basis.

Postoperative: liver biochemistry and coagulation profile on postoperative days 1, 3, 7, and day of discharge; postoperative morbidities according to Clavien–Dindo classification^22^; 30-day, 90-day, and in-hospital mortality; length of ICU and hospital stay; hospital readmission (90 days after discharge); and time to functional recovery (defined as independently mobile at the preoperative level, sufficient pain control with oral medication alone, ability to maintain at least 50 per cent daily caloric intake, no intravenous fluid administration, and no clinical signs of infection)^23^.

